## Abstract

**Background:**

Many medical situations necessitate a stressful period of waiting for potentially threatening test results. The medical waiting period is often associated with negative anticipatory anxiety and rumination about the outcome of treatment. Few evidence-based self-help coping interventions are available to assist individuals manage these periods. Theory and research suggest that positive reappraisal coping strategies may be particularly useful for this type of unpredictable and uncontrollable stressful context. The objective of this study is to investigate the effects of a Positive Reappraisal Coping Intervention (PRCI) on psychological well-being of women waiting for the outcome of their fertility treatment cycle.

**Methods/Design:**

In a three-armed randomized controlled trial, the effectiveness of the PRCI will be tested. Consecutive patients undergoing in vitro fertilisation in a Dutch university hospital and meeting selection criteria will be invited to participate. Those who agree will be randomized to one of three experimental groups (N=372). The PRCI Intervention group will receive the intervention that comprises an explanatory leaflet and the 10 statements designed to promote positive reappraisal coping, to be read at least once in the morning, once in the evening. To capture the general impact of PRCI on psychological wellbeing patients will complete questionnaires before the waiting period (pre-intervention), on day ten of the 14-day waiting period (intervention) and six weeks after the start of the waiting period (post-intervention). To capture the specific effects of the PRCI during the waiting period, patients will also be asked to monitor daily their emotions and reactions during the 14-day waiting period. The primary outcome is general anxiety, measured by the Hospital Anxiety and Depression Scale. Secondary outcomes are positive and negative emotions during the waiting period, depression, quality of life, coping and treatment outcome. During recruitment for the RCT it was decided to add a fourth non-randomized group, a PRCI Control group that received the PRCI and completed the questionnaires but did not complete daily monitoring.

**Discussion:**

Positive reappraisal is one of the few ways of coping that has been shown to be associated with increased wellbeing during unpredictable and uncontrollable situations like medical waiting periods. A simple evidence based self-help intervention could facilitate coping during this common medical situation. This RCT study will evaluate the value of a self-help coping intervention designed for medical waiting periods in women undergoing fertility treatment.

**Trial registration:**

The study is registered at the Clinical Tials.gov (NCT01701011).

## Background

The diagnosis and treatment of various medical conditions requires patients to wait for results that are potentially threatening to their well-being (e.g., breast biopsy results, pregnancy test results after fertility treatment, genetic screening outcomes) [1]. The outcomes of these tests are often unpredictable and often cause high levels of anticipatory anxiety and uncertainty [2] that are difficult to cope with. As the outcome of the medical tests or procedures for which patients are waiting cannot be changed or controlled, there is little point for the patient in trying to alter the situation. Instead, coping efforts should be directed at regulating the negative anticipatory emotions associated with waiting (e.g., feeling nervous, tense, worried, anxious) [3]. Despite the pervasiveness of medical waiting periods, few studies have investigated coping interventions to manage this stressful medical context [4].

Meaning-based coping strategies have been observed to be effective in contexts that involve a sustained period of unpredictability and uncertainty. Tedlie Moskowitz et al. [5] and Folkman and Moskowitz [6] observed that even in very stressful and uncertain situation such as caring for a terminally ill partner participants reported experiencing positive feelings. One type of coping strategy associated with these positive psychological states was positive reappraisal coping, which helped the person to redefine the situation in a more positive way, allowing them to derive some benefit from the negative experience. Folkman and Lazarus [3] proposed that these positive emotions had an important role in motivating people to continue in their efforts to cope in these ongoing stressful situations.

Fertility treatment is an example of a medical context that requires patients to wait for several weeks for the outcome of their treatment. The use of Assisted Reproductive Techniques (ART) (e.g., In Vitro Fertilization (IVF) and IntraCytoplasmic Sperm Injection (ICSI)) continues to increase and worldwide the total number of babies born through IVF is now exceeds 5 million [7].

A cycle of in vitro fertilisation typically requires nine to 12 days of self-injection with potent fertility drugs to stimulate the production of oocytes (eggs), retrieval of oocytes via trans-vaginal ultrasonography, fertilisation of oocytes in the laboratory with partner or donor sperm, and transfer of the resulting embryo to the uterus. Couples then wait two weeks to find out whether implantation and a pregnancy have occurred. Women often report that IVF/ICSI is an emotional and physical burden that can cause anxiety and stress [8,9]. The aspects most frequently reported as stressful are the fourteen-day waiting period between embryo transfer and the pregnancy test, and being informed that the treatment was unsuccessful [8-12]. Symptoms of anxiety and depression have been shown to increase during the waiting period after ET [1,2,10,11]. The lack of control the patient has to influence outcome during this period has also been shown to contribute to the increase in distress [2].

Despite the emotional stress reported during fertility treatment, many women do not seek professional support [13,14]. The stated reasons for this are often practical, such as the costs of counselling, distance to the appointment or being unsure how to arrange an appointment [13]. Nevertheless, women still worry about the impact of stress on the outcome of treatment and available meta-analyses are inconclusive on such effects [15,16]. A meta-analysis of 31 prospective studies found a small but significant association between stress, distress and reduced pregnancy chances [15]. Another meta-analysis of 14 prospective studies found no significant effect of emotional distress on the chance of becoming pregnant [16]. Several psychosocial interventions designed to support women with infertility have been described [17,18]. However, these are mostly aimed at providing general support throughout the entire fertility treatment and not at a specific point in the treatment, such as the waiting period. The impact of psychosocial interventions on anxiety, depression, coping and treatment outcome is inconsistent across reviews. One review of 25 studies concluded that psychosocial interventions reduced negative affect such as anxiety and infertility-specific distress but had no effect on pregnancy rates [17]. A subsequent meta-analysis of 22 studies concluded that psychotherapy was effective in reducing anxiety delivered in individual and group format [19]. The pregnancy rate with assisted reproductive techniques (ART) was similar in individual and group therapy however there was a difference in pregnancy rates between psychotherapy (45%) and the control group (14%) [19]. A final meta-analysis of 21 controlled studies showed that psychosocial interventions did not impact any form of psychological distress but the meta-analysis for pregnancy rate was significant with sub-group analysis showing increased pregnancy rate but only in patients undergoing non-ART treatments [18]. Inconsistent results could be due to interventions being too general. Indeed, Boivin [17] found that interventions with a strong educational and skills component that focused on specific targets (e.g., coping training, sex during fertile period) were more effective than those focused primarily on emotional expression and support.

The Positive Reappraisal Coping Intervention (PRCI) was designed to address unmet coping needs during medical waiting periods such as waiting for fertility treatment results. During the stressful waiting period after ET, women do not normally attend a clinic for tests or procedures and therefore lose the opportunities they had to receive informal support from the medical staff, clinic or other patients undergoing treatment at the same time [1]. Individual counselling of women during the waiting period is often not possible for hospitals because of the time investment and costs [13]. The PRCI is self-administered and comprises an explanatory leaflet describing this method of coping and ten statements designed to promote positive reappraisal coping. PRCI was conceptualised from the cognitive model of stress and coping [20,21] and developed according to the Medical Research Council framework for developing complex interventions [1]. Lancastle and Boivin [1] investigated the acceptability and feasibility of the intervention in an RCT of 55 women who used PRCI during the waiting period of an IVF/ICSI cycle versus a control group reading ten control positive statements. Results showed that the PRCI group rated the intervention as more helpful and suitable for the IVF/ICSI situation, more able to help women feel positive as well as better in sustaining positive reappraisal coping strategies during the waiting period. A feasibility study in the Netherlands showed that it is possible to recruit the amount of women necessary for the RCT in two years. Furthermore, the majority of the 27 women included in the study found the PRCI was suitable and feasible. (unpublished data, [name]). These results suggest that PRCI could be useful for medical waiting periods. However, its effectiveness on general or treatment-specific anxiety has not yet been systematically evaluated in a randomized controlled trial.

## Methods/Design

The PRCI will be evaluated in a three-arm Randomized Controlled Trial (RCT). Participants will be randomized to an intervention, monitoring control group or routine care. To capture the general impact of the PRCI all three groups will complete questionnaires at three time points: just before the waiting period (Time 1: pre-intervention), on Day 10 of the 14-day waiting period (Time 2: intervention) and 6 weeks after the start of the waiting period (Time 3: post-intervention). Table 1. Mobile phone text reminders will be sent to patients about completing the Time 1 and Time 3 questionnaires (if necessary) and all patients will receive a reminder just prior to the Time 2 assessment on the ninth day of the waiting period.

**Table 1 T1:** Measurement timetable according to group

**Measurements**	**T1 hCG to Embryo transfer**	**T2 Day 10 waiting period**	**T3 Six weeks after ET**
**BIF**	1,2,3,4	------	------
**HADS**	1,2,3,4	1,2,3,4	1,2,3,4
**FertiQol**	1,2,3,4	1,2,3,4 (Treatment only)	1,2,3,4 (non-pregnant group only)
**WCQ**	1,2,3,4	1,2,3,4	1,2,3,4
**DRK one day**	1,2,3,4	3,4	------
**IEF**	------	1,4	------
**DRK daily**	------	1,2	------
**Medical chart review**	------	------	1,2,3,4

Note. Numbers refer to group: 1 = PRCI Intervention, 2 = Monitoring Control, 3 = Routine Care and 4 = PRCI Control (non-randomized). BIF = Background Information Form, HADS = Hamilton Anxiety and Depression Scale, FertiQol = The Fertility Quality of Life, WCQ = Ways of Coping Questionnaire, DRK = Daily Record Keeping, IEF = Intervention evaluation form.

To capture the specific impacts of PRCI on the waiting period the intervention group will rate daily their emotions and reactions during the 14-day waiting period. Daily monitoring has previously been shown to be an efficient and sensitive way of evaluating emotional reactions during fertility treatment [2,9] and to be sensitive to intervention effects during ART [22]. One potential drawback of this method of assessment is that it may impact on the reporting of emotions itself. For example, habituation or sensitisation to monitoring per se may decrease or increase reporting of anxiety compared to groups that do not monitor [23]. Due to this potential reactivity the monitoring control group will also monitor emotions and reactions daily during the waiting period. The routine care control group will not receive the intervention or monitor reactions.

During recruitment for the RCT it was decided to add a fourth non-randomized group. The decision to add this group was based on preliminary results of on-going qualitative research with the PRCI and daily monitoring among women who had experienced miscarriages (unpublished data, [name]). The women in the miscarriage study reported that the daily monitoring had an effect on their emotions in that it helped them take account of the impact of miscarriages on their emotional lives. If daily monitoring was itself an intervention then it could attenuate, heightened or obscure effects of the PRCI intervention in unknown ways. Therefore it was decided to add a PRCI Control group that received the PRCI and completed the questionnaires but did not complete daily monitoring.

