### Objective

The aim of this study is to investigate the effect of the PRCI on psychological well-being of women waiting for the results of an IVF/ICST treatment. The primary outcome is level of general anxiety measured before the waiting period (pre-intervention), on day ten of the 14-day waiting period (intervention) and six weeks after the start of the waiting period (post-intervention). Secondary outcomes are positive and negative treatment emotions during the waiting period, depression, coping style, quality of life and treatment outcome.

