### Hypotheses

The PRCI increases the use of positive reappraisal coping strategies and reduces symptoms of general anxiety and depression, improves quality of life across assessment (pre intervention, intervention and post intervention) as well as increases positive and decreases negative emotions during the fourteen days of the waiting period in patients undergoing an IVF/ICSI treatment.

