### Study measures

Data will be obtained with self-reported questionnaires, daily monitoring and from the treatment medical records. Table 1 shows the assessment timetable. Questionnaires will be completed prior to, during and after the intervention whereas monitoring will be daily during the two-week waiting period. The following self-report measures will be used:

The Background Information Form (BIF) is a 16-item questionnaire to measure demographic (e.g. age, educational status), medical (e.g. previous illness) and gynaecological (e.g. infertility diagnosis, previous infertility treatment) characteristics as well as treatment expectations (e.g. chances of conceiving, perceived control over the outcome).

The Hospital Anxiety and Depression Scale (HADS) will be used to measure general anxiety and depression. The HADS consists of 14 items (7 items for each subscale) that are rated on a 4-point Likert scale. The total score is the sum of the 14 items, and for each subscale the score is the sum of the respective seven items (ranging from 0–21). Scores on each scale can be interpreted in ranges: normal (0–7), mild (8–10), moderate (11–14) and severe (15–21). The Dutch version of the HADS has been shown to be a valid and reliable instrument [28].

The Fertility Quality of Life (FertiQoL) scale will be used to measure the impact of infertility and its treatment. FertiQoL consist of 36 items that assess core (24 items) and treatment related quality of life (10 items) and overall life and physical health (2 items). Items are rated on a 5-point response scale. Cronbach reliability coefficients for the Core and Treatment FertiQoL were 0.92 and 0.81, respectively [29]. The convergent validity of the Dutch version of the FertiQoL has been investigated and shows similar reliability [30]. Items are summed and scaled, with a range of 0 to 100. Higher scores indicate better quality of life.

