A medical chart review at the end of treatment will be used to obtain treatment data and will include the total number of past IVF/ICSI stimulated and cryopreserved cycles, past intrauterine insemination cycles, previous conceptions/births, infertility diagnosis, smoking status, alcohol use, and body mass index. Data about the current treatment will include: type of treatment and protocol, date of first and subsequent treatment attempt, treatment cancellation (yes/no) and reason for cancellation, number of oocytes retrieved, total number of embryos created, transferred and cryopreserved, treatment outcome (positive pregnancy test, clinical pregnancy, live birth), physician recommendation for next cycle and patient compliance with physician recommendation”.

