### Statistical analysis

IBM SPSS Statistics will be used to perform the statistical analysis. Equivalence of baseline measures between groups will be examined by one-way analyses of variance (ANOVA) for normally distributed variables on interval or ratio level, chi-square for normally distributed variables on nominal level and Kruskal Wallis *H* test for normally distributed variables on ordinal level. If study variables are not normally distributed then data will be transformed to normalise (e.g., square root, log, etc. as is required). If the groups are not comparable on demographics, medical history or gynaecological variables, those variables will be employed as covariates in subsequent analyses. To examine the differences between groups over time a repeated measure mixed factorial ANOVA design will be used for variables on interval or ratio level. To compare the fourth group with the three separate groups also an ANOVA design will be used. Intention to treat and multi-level modelling will be used to analyse the data to take account of attrition.

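### The quality-of-life hypothesis spans three assessments, but the FertiQoL schedule gives no core score at T2 and no scores from pregnant women at T3, so a three-time-point analysis is impossible (core) or not a randomised comparison at T3 (treatment scale)

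*Protocol article*

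**What the plan says.** Objective lists the secondary outcomes, including "depression, coping style, quality of life and treatment outcome". Hypotheses states that the intervention "improves quality of life across assessment (pre intervention, intervention and post intervention".

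Study measures describes FertiQoL as a 36-item instrument whose items "assess core (24 items) and treatment related quality of life (10 items", plus two general items. Core and Treatment have separate reliability coefficients.

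Table 1 in Methods/Design schedules FertiQoL for all groups without restriction at T1, as "1,2,3,4 (Treatment only" at T2 (day 10) and as "1,2,3,4 (non-pregnant group only" at T3 (six weeks).

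Statistical analysis says that, for differences between groups over time, "a repeated measure mixed factorial ANOVA design will be used for variables on interval or ratio level". It adds: "Intention to treat and multi-level modelling will be used to analyse the data to take account of attrition". Neither sentence makes an exception for FertiQoL.

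Randomization places allocation after T1 and before embryo transfer. Study measures says the chart review will record "treatment outcome (positive pregnancy test, clinical pregnancy, live birth".

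**The concern.** Hypothesis, schedule and analysis are each stated, and they do not fit together. A repeated-measures analysis over three times needs the same scale from the same population each time. For FertiQoL, the scale changes at T2 and the population changes at T3.

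The change of population matters more. Who answers at T3 depends on an event that happens after allocation and that the trial counts among its outcomes. Women still non-pregnant in one group need not resemble women still non-pregnant in another, even if the pregnancy rates are equal. A group difference at T3, or a group-by-time interaction that draws on T3, would mix any effect of the intervention with selection. The balance that randomisation gives would be lost for that part of the quality-of-life result.

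**Working it through.** **Step 1. Scores that the schedule allows** (Table 1 read with Study measures, taking the T2 note to mean the treatment items)

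| Scale | T1 | T2 | T3 | All three times |
|---|---|---|---|---|
| Core (24 items) | all women | not given | non-pregnant | nobody |
| Total, needing core items | all women | not given | non-pregnant | nobody |
| Treatment (10 items) | all women | all women | non-pregnant | non-pregnant only |

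**Step 2. Is the T3 restriction post-randomisation?** Allocation precedes embryo transfer, so pregnancy status is settled after allocation. Treatment outcome is also a listed secondary outcome. The T3 set is therefore selected on a post-randomisation outcome.

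**Step 3. Is T2 affected?** T2 is day 10 of a 14-day wait and is scheduled for every group whatever the later result. The T1-to-T2 treatment-scale comparison does not condition on pregnancy.

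**Step 4. What the two planned methods would do**

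- A complete-row repeated-measures ANOVA over T1, T2 and T3 keeps only women with T3 scores. It discards pregnant women's T1 and T2 scores.
- A multi-level model keeps those scores. It would, however, handle a form withheld by design as if it were attrition. Its T3 estimate would rest on non-pregnant women, in effect assuming that pregnant women with similar earlier scores would have answered alike.

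**Step 5. Size**

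Inputs from Sample size: 99 evaluable women per group, 297 in total, 20% attrition. The inflation reproduces: 99 / (1 − 0.20) = 123.75, rounded up to 124, and 3 × 124 = 372. The 297 was set for anxiety, with an effect given only as medium. It can be neither confirmed nor called wrong, and this point does not depend on it.

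The protocol gives no expected pregnancy rate p, so p is an assumption. Women per group with T3 FertiQoL = 99 × (1 − p), rounded down to n. Illustrative power is for a three-group F test at α = 0.05 with an assumed f = 0.25, N = 3n, and noncentrality 0.25² × N.

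| Assumed p | n per group | N | Noncentrality | Power |
|---|---|---|---|---|
| 0% | 99 | 297 | 18.6 | 98% |
| 20% | 79 | 237 | 14.8 | 94% |
| 30% | 69 | 207 | 12.9 | 90% |
| 40% | 59 | 177 | 11.1 | 85% |
| 50% | 49 | 147 | 9.2 | 77% |

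The loss of power is modest over most of this range.

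For scale on the selection side, Background cites one meta-analysis with pregnancy rates of 45% under psychotherapy and 14% in controls. If two groups here differed that much, 99 × 0.55 ≈ 54 and 99 × 0.86 ≈ 85 women would remain. This is an extreme illustration: Background also cites null results, and the protocol hypothesises no effect on pregnancy.

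**The case against.** The strongest reply is that Statistical analysis is a general sentence in a condensed article. It does not spell out a three-time-point FertiQoL model, and the choice of scale and time points for each secondary outcome can be left to an analysis plan that is not shown. It also promises multi-level modelling, which does not need complete rows. Giving an infertility-specific questionnaire only to women who are not pregnant may be sensible. The hypothesis names no FertiQoL scale, so a Treatment score at T2 is a fair test of it at the intervention assessment.

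Much of this stands, and it rules out four stronger readings that a reader might infer:

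- *That the whole quality-of-life analysis is conditioned on pregnancy.* The T1-to-T2 treatment comparison is not.
- *That the core scale is unusable.* A T1-to-T3 core comparison in non-pregnant women remains possible.
- *That pregnant women's T1 and T2 scores will be lost.* This follows only from a complete-row ANOVA, and the document also plans a multi-level model.
- *That T3 results will be presented as applying to all patients.* Nothing says so, and Table 1 labels the restriction openly.

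The conflict itself survives. The hypothesis covers the post-intervention assessment without restriction, while the schedule excludes women who conceive. The multi-level sentence is aimed at attrition, which this is not. No later analysis plan can supply core scores at T2 or FertiQoL scores from pregnant women at T3 if they are not collected.

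**Conclusion.** The point holds in limited form. On the stated schedule, a three-time-point analysis of the core or total FertiQoL is impossible. A three-time-point analysis of the treatment scale has T3 data only from women selected on a post-randomisation outcome, so contrasts involving T3 are not randomised comparisons under either planned method.

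The direction and size of any bias at T3 are not shown and cannot be derived from the document. Material bias would require the intervention to affect pregnancy or to change which women remain non-pregnant. The sample and power figures rest on an assumed pregnancy rate and an assumed f = 0.25.

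The consequence is confined to a secondary outcome. HADS, which carries the primary outcome, is scheduled for all groups at all three times. The mismatch should be corrected, but it does not threaten the main result.

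**What to change.** 1. Make the randomised quality-of-life comparison the T2 Treatment FertiQoL in all women randomised to the three arms, adjusted for T1 Treatment FertiQoL.
2. Analyse T3 FertiQoL, core and treatment, separately with T1 as baseline and outside the repeated-measures model. Label it a non-randomised comparison in non-pregnant women.
3. Reword the quality-of-life hypothesis to match. For example: the intervention improves treatment-related quality of life during the waiting period; quality of life afterwards is examined only in women who are not pregnant.

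This changes wording and analysis only and uses data already scheduled. The cost is that the trial makes no all-patient claim about quality of life after the waiting period, which the schedule cannot support in any case.
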